## Abstract

**Background:**

Following admission to a nursing home, the feelings of depression and burden that family carers may experience do not necessarily diminish. Additionally, they may experience feelings of guilt and grief for the loss of a previously close relationship. At the same time, individuals with dementia may develop symptoms of depression and agitation (BPSD) that may be related to changes in family relationships, social interaction and stimulation. Until now, interventions to alleviate carer stress and BPSD have treated carers and relatives separately rather than focusing on maintaining or enhancing their relationships. One-to-one structured activities have been shown to reduce BPSD and also improve the caring experience, but barriers such as a lack of resources impede the implementation of activities in aged care facilities. The current study will investigate the effect of individualised activities based on the Montessori methodology administered by family carers in residential care.

**Methods/Design:**

We will conduct a cluster-randomised trial to train family carers in conducting personalised one-to-one activities based on the Montessori methodology with their relatives. Montessori activities derive from the principles espoused by Maria Montessori and subsequent educational theorists to promote engagement in learning, namely task breakdown, guided repetition, progression in difficulty from simple to complex, and the careful matching of demands to levels of competence. Persons with dementia living in aged care facilities and frequently visiting family carers will be included in the study. Consented, willing participants will be randomly assigned by facility to a treatment condition using the Montessori approach or a control waiting list condition. We hypothesise that family carers conducting Montessori-based activities will experience improvements in quality of visits and overall relationship with the resident as well as higher self-rated mastery, fewer depressive symptoms, and a better quality of life than carers in the waiting list condition.

**Discussion:**

We hypothesise that training family carers to deliver personalised activities to their relatives in a residential setting will make visits more satisfying and may consequently improve the quality of life for carers and their relatives. These beneficial effects might also reduce nursing staff burden and thus impact positively on residential facilities.

**Trial Registration:**

Australian New Zealand Clinical Trials Registry - ACTRN12611000998943

## Background

Both people with dementia and their family carers may suffer from the consequences of dementia such as confusion, disorientation and reduced language fluency. As a result, people with dementia may experience increasing difficulty in communicating their needs to family and professional caregivers for physical comfort, social engagement and meaningful activity. According to the *unmet needs theory *[1], the resulting distress contributes to the behavioural and psychological symptoms of dementia (BPSD). The psychological symptoms include anxiety, depression, hallucinations and delusions. Behavioural symptoms include restlessness, aggression and calling out. BPSD reach a peak in the middle to late phases of dementia and greatly increase the likelihood of admission to an aged residential facility [2]. Within facilities, rates of BPSD are often high. In 11 Sydney nursing homes, for example, 60% of residents had an affective disorder, 53% showed activity disturbance and 77% were aggressive [3].

When BPSD stem from pain, co-morbid major depression or psychosis, treatment with analgesics, antidepressants or antipsychotics can bring relief. However, in cases where the causes of BPSD are less obvious, medications have variable efficacy and can lead to adverse effects such as worsened confusion and falls [4,5]. More attention is being paid, therefore, to non-pharmacological interventions that better address the needs that underpin BPSD. In two recent systematic reviews, it was demonstrated that treatments such as music, recreation therapy and relaxation therapy significantly reduced BPSD with effect sizes ranging from 0.5 to 1.15 [6,7]. The largest effects were found when treatments were tailored to individuals' own backgrounds, interests and skills.

Two studies conducted since the reviews suggested that Montessori-based activities significantly reduced agitated behaviours and increased positive mood and engagement [[8], van der Ploeg ES, Eppingstall B, Camp CJ, Runci S, Taffe J, O'Connor DW. The effect of personalised, one-to-one interaction using Montessori-based activities on agitation, engagement and mood in aged care facility residents with dementia. Submitted]. Montessori-based activities follow the principles espoused by Maria Montessori and subsequent educational theorists who promoted engagement in learning by sequencing tasks from simple to complex; providing cues to successful completion; encouraging repetition, and carefully matching demands to individuals' interests and levels of competence [9,10]. For people with dementia, Montessori-type programs entail detailed interviews with family carers about the resident's former interests and skills coupled with assessments of cognitive, language and motor skills. A range of activities are then presented, tested and refined. When dementia is advanced, the activities are simple (e.g. completing a jigsaw made from a family photograph). Facilitators present tasks deliberately, modelling them first and using little language if appropriate. The main objective is to engage participants' interest and involvement. Despite a growing evidence base, personalised one-to-one activities are rarely implemented in aged care facilities as they require extra time and resources that are often not available.

Dementia may also inflict negative consequences for family members of the individual with dementia [11]. Frequently reported adverse consequences of caring for relatives with dementia include physical health problems, depression, social isolation and financial burden [12]. These stresses might be expected to diminish following admission to a residential facility where care tasks are undertaken by paid staff. In reality, stress levels often remain high, with only a change in the source of burden [13,14]. New stressors may include the practicalities of visiting, tension with staff regarding care roles, concerns about care and continuing costs [15]. Carers possibly also experience guilt and difficulties relinquishing their role as primary supporter [16,17]. In addition, visits to the facility can prove unsatisfying, especially if the resident is anxious, agitated and increasingly more confused. There are fewer opportunities for easy communication, shared activities and contentment in the relationship [18,19]. Interventions to ease this transition have included carer education and support groups [20]. While promising, they considered the family carer and resident separately, overlooking the loss of relationship between the two, particularly significant for spouses [15,21]. Preserving and enhancing this relationship through meaningful activities can restore a sense of competence and self-determination for family carers [22] and improve the well-being of both parties [23]. An activity program delivered by family carers to relatives with dementia living in the community resulted in large increases in carers' confidence through perceived enhanced skills and personal control as well as enhanced engagement and mood of the individuals with dementia [24].

Interventions to alleviate carer stress and BPSD have mostly treated carers and relatives separately rather than focusing on re-establishing and enhancing their relationship. Since one-to-one structured activities have been shown to reduce BPSD and also improve the caring experience, they seem an ideal intervention to bring people together and thus improve wellbeing for both carers and their relatives with dementia. The current study will investigate the effect of individualised activities based on the Montessori methodology administered by family carers in residential care on the wellbeing of carers. We hypothesise that family carers conducting Montessori-based activities will experience higher self-rated mastery, fewer depressive symptoms, and a better quality of life than carers in a waiting list period, as well as a better quality of visits and overall relationship with the resident.

## Methods/Design

### Study design

We will employ a cluster-randomised trial to allocate a condition (treatment vs. waiting list) at facility level. The project protocol has been approved by the ethical committees of Monash University and Southern Health.

### Study protocol

The study period will be brief to reduce the likelihood that changes in outcomes are due to dementia progression, inter-current illness or other incidental events. Activity sessions must be long enough to detect changes in selected outcomes during the carer's visit, but not so long that sessions are likely to be interrupted by meals or nursing interventions. In our recently completed Montessori study [25], the choice of 30-minute sessions has worked well. A study period of up to four weeks has also proved feasible. We will therefore employ an exposure of six sessions spread over a three week period for both conditions. The choice of condition (treatment or control) will be randomly determined using Excel. The program from week 1 (W1) to week 5 (W5) is shown in Table 1. Baseline measures will be conducted at the start of the Montessori workshop or dementia education session (W1). All participants will receive a follow-up phone call half way through W2-W4 to ascertain they have filled out questionnaires after each visit. A face-to-face appointment will be made to complete the final measurements at the end of W4.

**Table 1 T1:** Program for treatment and control condition groups

	Treatment group	Control group
W1	Group Montessori workshop	Dementia education session

	↓	↓

W2 W3 W4	6 Montessori sessions	Waiting list period

		↓

W5		Group Montessori workshop

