### Ethical considerations

A facility staff member will identify potential residents and their carers and seek agreement from the carer to be contacted by the research team. Since the residents concerned will have dementia, often to a moderate or severe degree, the family carer (or significant other person) who visits most frequently will be asked for written informed *consent*, on his/her own behalf and on behalf of the person with dementia, in accordance with both the Monash University HREC and the Victorian Civil and Administrative Tribunal. Persons with dementia must also *assent *to participate in the study. If it is clear from their demeanour or behaviour that they do not wish to participate, their participation in the study will be discontinued.

Carers will either directly commence with the Montessori training and implementation or will be told that due to limited resources they will be put on a waiting list for four weeks (the control condition). We will ask them to complete the baseline and all follow-up measures and to attend a dementia education session. Carers will be blinded to the hypotheses of the study and the purpose of the waiting list option. After the carers in this condition complete the measurements associated with the control period, they will be debriefed regarding the purpose of the waiting list option and are invited to participate in a Montessori workshop.

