### Recruitment

Aged care facilities will be contacted by telephone to explain the studies. If facilities show interest in the study, researchers will visit the facility to provide all relevant parties (director of nursing, nursing staff and diversional therapists) with more detailed information. If facilities consent to participate in the study, a pre-selection screening will be conducted to identify eligible participants. An appointed delegate of the facility will then contact the identified family carers to ask if they consent with forwarding their contact details to a Monash University researcher. When verbal consent is given a senior researcher will contact the carer to explain the study and answer queries. If carers express interest in the studies they will be sent a Participant Information and Consent Form package. Once written consent is received, researchers will gather baseline information and plan the training session with groups of up to six participants. If more than six family carers are eligible and interested in the study in a particular facility, more training sessions will be organised.

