### Experimental conditions

#### Montessori-based activities

Family carers will be trained in the principles underpinning Montessori activities in three-hour group sessions in their relative's facility. A pair of researchers will conduct these workshops. They will spend half an hour helping carers to fill out the baseline questionnaires; an hour explaining the theoretical basis of Montessori activities in dementia, and an hour and a half in smaller groups brainstorming and practising possible activities.

Carers will choose up to 10 activities based on their relative's former interests and current motor and language skills. For the purpose of continuity of the intervention after the study finishes, carers will be asked to prepare materials using their own and the facilities materials. The mode of delivering activities can be easily adapted to residents' cognitive status, making it possible to include people with mild through to very severe dementia. For example, a suitable activity for a former mechanic with moderate dementia might include discussing the characteristics and qualities of period cars shown in laminated photographs. If dementia is severe, the activity can be simplified to sorting the photographs into categories based on colour, or preference.

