#### Control condition

The control condition should match the level of contact with the researchers and additionally control for the effects of the carers meeting each other as part of the group training. To ensure comparability with the experimental condition, the family carers will receive a dementia education session lasting three hours. Again, the first half hour will be spent filling out the baseline questionnaires; an hour and a half will be used for dementia education after which the groups will split into smaller groups to discuss the material just presented. To match the involvement of the relatives with dementia, we will ask carers towards the end of the training session to spend some time with their relative. During this time, the researchers will spend time with every couple, introducing themselves to the residents and engaging in general conversation with them.

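### Carer self-report baselines are completed inside the allocated session, when carers may already know their condition; this exposes uses of baseline in the secondary analyses, not the primary ratings

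*Protocol article*

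**What the plan says.** Condition is allocated at facility level (Study design). On timing, the Study protocol section states: "Baseline measures will be conducted at the start of the Montessori workshop or dementia education session (W1". The two session descriptions agree. For the workshop, Montessori-based activities says of the pair of researchers: "They will spend half an hour helping carers to fill out the baseline questionnaires". For the education session, Control condition says "the first half hour will be spent filling out the baseline questionnaires".

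On what carers know, Ethical considerations says that carers either go straight into Montessori training or "will be told that due to limited resources they will be put on a waiting list for four weeks". The next sentence, about the wait-listed carers, reads: "We will ask them to complete the baseline and all follow-up measures and to attend a dementia education session". The blinding is limited: "Carers will be blinded to the hypotheses of the study and the purpose of the waiting list option".

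Secondary measures lists the carer outcomes recorded both at baseline and at the end of the three weeks: relationship quality, mastery, CES-D and Carer-QoL. Other measures adds pre-morbid relationship quality as a baseline item, and Statistical analysis gives that item as its example of an ANCOVA covariate.

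**The concern.** A baseline is useful in a randomised comparison because allocation cannot have influenced it. Here the questionnaires are completed after the facility has been allocated, in a session whose type depends on the arm, by people who are not described as blind to their own condition. A carer just told to wait for lack of resources, or one arriving to be trained, may answer questions about mood, mastery or closeness differently from the same carer a week earlier.

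Three uses of baseline are exposed:

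- **Comparability.** With 50 carers allocated by facility, baseline is the main evidence on whether the arms started alike. If taken after disclosure, it cannot separate chance imbalance from reaction to allocation.
- **Covariates.** Pre-morbid relationship quality is a retrospective rating, presumably given by the carer, and may be coloured by the same reaction before it enters the ANCOVAs.
- **Change.** Any change-from-baseline or baseline-adjusted analysis of the secondary measures would carry a baseline shift into the estimated effect.

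**Working it through.** No figure in the article is in dispute here. The check is one of sequence, followed by an illustration on assumed values.

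**Sequence**

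1. Allocation is by facility, and W1 in Table 1 already holds different sessions for the two arms. Baseline within the W1 session therefore follows allocation.
2. Ethical considerations mentions the waiting-list notice first and the request to complete baseline second. That order, with arm-specific sessions, makes prior knowledge the natural reading. No sentence dates the disclosure.
3. Blinding covers the hypotheses and the reason for the waiting list, not the carer's own condition. Nothing stated protects the baseline answers.

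**Which analyses are affected**

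Let x be the shift in the between-arm baseline difference caused by knowing the allocation, p the part of that reaction still present at the end of the study, and r the baseline-to-end correlation, with equal SDs. In SD units the bias is:

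- end-of-study means only: p (x does not enter);
- change from baseline: p − x;
- baseline-adjusted: p − r·x.

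For another baseline covariate, such as pre-morbid relationship quality, the last line applies with r as its correlation with the outcome. The primary ratings are made after each visit and have no described baseline, so x does not enter there.

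**Illustration (assumed: p = 0, no true effect, no clustering, two-sided 0.05)**

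From Sample size calculation, 50 recruited less 20% leaves 50 × 0.8 = 40, or n = 20 per arm if equally split. The noncentrality is x / [√(2(1 − r)) · √(2/n)] for the change score (38 df) and, approximately, r·x / [√(1 − r²) · √(2/n)] for the adjusted contrast (37 df). For r = 0.5 and x = 0.2 these are 0.2/(1 × 0.316) = 0.63 and 0.1/(0.866 × 0.316) = 0.37.

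| x (SD) | r | Change-score bias, absolute (SD) | False-positive rate | Adjusted bias, absolute (SD) | False-positive rate |
|---|---|---|---|---|---|
| 0.2 | 0.5 | 0.20 | 0.095 | 0.10 | 0.065 |
| 0.2 | 0.7 | 0.20 | 0.125 | 0.14 | 0.093 |
| 0.2 | 0.8 | 0.20 | 0.164 | 0.16 | 0.131 |
| 0.3 | 0.5 | 0.30 | 0.152 | 0.15 | 0.083 |
| 0.3 | 0.7 | 0.30 | 0.223 | 0.21 | 0.148 |
| 0.3 | 0.8 | 0.30 | 0.310 | 0.24 | 0.235 |

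For scale, the planned effect is (3.48 − 2.89)/0.74 = 0.80 SD.

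**Comparability check**

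With 25 carers per arm at baseline, the standard error of a baseline difference is √(2/25) = 0.28 SD before clustering. A shift of 0.2 to 0.3 SD is therefore the size of ordinary chance imbalance and could not be recognised as a reaction to allocation.

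**Direction**

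On a scale where higher is better, disappointment lowering control baselines or anticipation raising treatment baselines would shrink the apparent gain. Reactions the other way would inflate it. The article supports neither.

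**The case against.** The case on the other side has several parts, and most of it stands as a limit on the point.

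- **Disclosure is not dated.** A reader might infer that carers have definitely been told their condition before they complete the forms. The text does not say so. Ethical considerations describes what carers are told, not a timetable, and the forms come at the very start of the session. The notice could follow the forms. What remains is that the text does not secure that order and its wording points the other way.
- **The stated analysis may not use baseline outcomes.** Statistical analysis compares means by t-test and ANOVA and names neither a change score nor adjustment for an outcome's own baseline. For end-of-study means a baseline shift does no harm. This stands. The exposure is confined to the named type of covariate, the comparability check, and any use made of the two-time-point secondary measures.
- **The primary outcome.** A reader might extend the point to quality of visits. That is not supported, because those ratings have no baseline.
- **Recruitment.** One might read "Once written consent is received, researchers will gather baseline information and plan the training session with groups of up to six participants" as contradicting the in-session timing. It need not: Other measures lists demographics, visiting pattern, file data and staff-completed ratings that could be gathered then. No contradiction is shown.
- **Help with the forms.** It is tempting to say that the researchers delivering each session assist in both arms. Help is documented only for the Montessori workshop; the control description is silent.
- **Mitigation.** Hypothesis blinding, a matched three-hour control session and the promise of a later workshop lessen the risk. They do not remove it.
- **Persistence.** If the reaction lasts to the end of the study (p = x), a late baseline cancels it in a change score, whereas an early baseline leaves p in. This is correct: the fix does not cure unblinded self-report at follow-up. But p is then part of every end-of-study comparison as well, and an early baseline at least is not itself affected by allocation.

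**Conclusion.** The point holds in limited form. The carer self-report baselines are fixed inside an arm-specific session after allocation, and nothing stated shields them from knowledge of condition. Baseline comparability checks, carer-rated covariates in the ANCOVAs, and any change or baseline-adjusted analysis of the secondary measures can be biased. The primary per-visit ratings and simple end-of-study comparisons are not.

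Size and direction cannot be derived from the article. The tabulated values rest on an assumed shift and correlation, 20 completers per arm, no clustering and a reaction that affects baseline only; they show what is possible, not what is expected. The conclusion also assumes the natural reading of when carers learn their condition, and that pre-morbid relationship quality is rated by the carer. It is worth correcting because a distorted baseline cannot be repaired in the analysis and the change is cheap.

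**What to change.** State that the carer baseline questionnaires are completed and collected before the facility's condition is disclosed to carers. Either of two routes would do:

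1. take them at the post-consent contact described in Recruitment; or
2. invite all carers to a neutrally described three-hour session, collect the forms in its first half hour, and only then announce the content and, where it applies, the waiting list.

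Specify the same level of researcher help with the forms in both arms. Bring Study protocol, Ethical considerations, Montessori-based activities and Control condition into line with the chosen order; under the first route, Recruitment should say that its baseline information includes these questionnaires.

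The cost is a re-ordering of existing steps, with no added participants, measures or visits. The downside is small: the second route depends on neutral invitation wording, and under the first some forms will be completed with less help.
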